#### Randomization and blinding

To allocate participants to the study groups, a stratified block randomization method will be employed, based on the classification of gestational diabetes and type 2 diabetes. The block sizes will be either 4 or 6, and the allocation ratio will be 1:1. To ensure concealment of allocation, a central allocation method will be used. Specifically, certain participant information will be sent via text message to the supervisor, who will then communicate the participant’s group assignment. Regarding blinding, the study will be conducted as a single-blind study. Due to the nature of the intervention, participants, clinical caregivers, outcome assessors, and intervention providers will not be blinded to group allocation. However, efforts will be made to minimize bias during data analysis by blinding the data analyst to group allocation. This will be achieved through participant coding, preventing the analyst from accessing information about which participants belong to each group. By doing so, the analysis and interpretation of the data will remain impartial and unbiased.

#### Intervention

The intervention group will participate in an 8-week program consisting of group sessions held every 2 weeks, with each session lasting approximately two hours. These sessions will be led by a midwife who is a PhD student in midwifery and an obstetrician, and the group will consist of 2 to 10 women. The content of each session will be based on the curriculum and materials of the centering pregnancy program, which have been reviewed and approved by the obstetrician and nutritionist.

At the start of each session, the midwife, assisted by the researcher, will conduct measurements of weight, blood pressure, and blood glucose levels using a glucometer. This assessment process will take approximately 30 min. The remaining time, around 60 to 90 min, will be dedicated to group discussions focused on predetermined topics that are relevant to the participants’ needs.

Session 1: The first session will provide diabetes education, covering the risks of diabetes for both the mother and the fetus, the importance of self-monitoring, and nutrition education. This will include introducing food groups, emphasizing the significance of meal control, providing information on food labels, and facilitating discussions on pregnancy-related concerns and coping strategies.Session 2: The second session will continue with diabetes education, focusing on the importance of exercise. Additionally, there will be discussions on pregnancy-related topics such as pain relief during labor and addressing issues of intimate partner violence.Session 3: The third session will address postpartum diabetes and what to expect during the postpartum period. Participants will also receive information on the importance of glucose tolerance testing. Pregnancy-related topics will include discussions on expectations during labor and delivery, as well as contraception.Session 4: The fourth session will emphasize diabetes education related to lifelong health monitoring and the risk of diabetes for offspring. Additionally, there will be discussions on pregnancy-related topics such as newborn care, including sleeping, proper usage of car seats, and feeding (Table 1).

**Table 1 Tab1:** Curriculum for group prenatal care in women with diabetes

Sessions	Pregnancy Titles	Diabetes Titles
1	Introduction, discussion about expectations from the group, measurement of weight and blood pressure, concerns and normal pregnancy disorders, and coping strategies	Explanation of diabetes risks for mother and fetus and the importance of self-monitoring/introduction of food groups and the importance of meal control/introduction of food labels
2	Introduction, discussion about expectations from the group, measurement of weight and blood pressure, methods of pain relief during childbirth and intimate partner violence	Exercise
3	Introduction, discussion about expectations from the group, measurement of weight and blood pressure, what to expect during labor and delivery, prevention of pregnancy and breastfeeding	Diabetes after pregnancy and postpartum issues, and the importance of glucose tolerance test
4	Introduction, discussion about expectations from the group, measurement of weight and blood pressure, infant care (sleep/car seat/feeding)	Lifelong health monitoring and the risk of developing diabetes for children

The control group will receive standard care based on national guidelines.

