Centering Pregnancy is an innovative prenatal care model that involves grouping women with similar gestational ages for comprehensive care. This approach fosters behavior modification, social support, and the exchange of knowledge among participants. By creating a positive environment, pregnant women can learn from one another, gain a greater sense of agency over their pregnancies, and benefit from improved education and support. Centering Pregnancy stands out as a distinct and advantageous approach to providing prenatal care [15–17].

Currently, there is a research gap in evaluating the Centering Pregnancy group care model specifically for diabetes due to limited studies conducted in this area [18, 19]. Most of the existing studies have relied on observational designs [20–22], which may be susceptible to confounding factors. Moreover, the majority of studies have been conducted in other countries, particularly in the United States, and findings based on different racial and ethnic groups may not be directly applicable to Iranian women. However, it has been demonstrated that this model can reduce neonatal hospitalization costs by decreasing NICU admissions [23].

Therefore, given the adverse consequences of diabetes in pregnancy, implementing the Centering Pregnancy group care model has the potential to be beneficial in improving the healthcare system’s burden. To enhance self-care practices for pregnant women with diabetes and improve their pregnancy experience, as well as maternal and neonatal outcomes, it is essential to assess the current state of care and gather insights from these individuals using a comprehensive approach. This study will serve as the first investigation in Iran to implement and evaluate the Centering Pregnancy group care model in pregnant women with diabetes, employing a combined methodology to gather comprehensive data.

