### Data analysis

The data obtained will be analyzed using the double data entry approach in SPSS software version 24. Descriptive statistics, including frequency (percentage) for categorical data and mean (standard deviation) for normally distributed data, as well as median (interquartile range) for non-normally distributed data, will be used to describe socio-demographic and obstetrics characteristics. The normality of the data will be assessed using the Kolmogorov-Smirnov test.

In the bivariate analysis, ANCOVA and the chi-square test will be employed to compare the means of variables related to diabetes self-care activities, diabetes management self-efficacy, pregnancy experience, satisfaction with perinatal care, breastfeeding performance at 6 weeks postpartum, and the frequencies of preterm delivery, cesarean section delivery, and neonatal hospitalization between the two groups. In the multivariate analysis, the general linear model will be utilized, controlling for socio-demographic and obstetric characteristics, to further explore the relationships among the variables mentioned above.

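### Intervention women are treated in shared groups, but the named between-arm tests assume independent women, so standard errors are too small if outcomes correlate within groups

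*Protocol article*

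**What the plan says.** The Randomization and blinding section allocates individual women in strata by diabetes type: "The block sizes will be either 4 or 6, and the allocation ratio will be 1:1". Under Intervention, the treated women enter an "8-week program consisting of group sessions held every 2 weeks", and "the group will consist of 2 to 10 women". After the measurements, the rest of each session "will be dedicated to group discussions focused on predetermined topics". For the other arm, "The control group will receive standard care based on national guidelines", with no groups described. The Background gives the mechanism: "This approach fosters behavior modification, social support, and the exchange of knowledge among participants".

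The Data analysis section then states that "ANCOVA and the chi-square test will be employed to compare the means of variables". For the adjusted analysis, "the general linear model will be utilized, controlling for socio-demographic and obstetric characteristics". Neither sentence contains a term for the session group. The Sample size section gives means, SD, alpha, power and dropout, but no ICC, group size or design effect.

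**The concern.** This is a partially nested design: women are randomised one by one, then treated together in one arm and separately in the other. Women who talk through diet, exercise and glucose monitoring together may end up with similar scores. Fifty intervention women in a few groups would then carry less information than fifty independent women.

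ANCOVA, chi-square and the general linear model cannot see this. They would report standard errors that are too small, and an unusually good or poor group could be read as a treatment effect. All three primary outcomes are compared in this way. The article does not say that group membership will be recorded; if it is not, the problem can be neither corrected nor measured afterwards.

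**Working it through.** **The plan's own figure.** The Sample size section gives means of 3.1 and 3.7 and an SD of 1.2, so d = (3.7 − 3.1)/1.2 = 0.5. It states 45 per group, and 45/0.9 = 50 after dropout. The usual two-sample formula with these inputs gives 2 × (1.96 + 1.282)²/0.5² = 84.1, about 85 per arm, so the stated 45 is not reproduced. That is a separate matter. What matters here is that, with independent women, power at d = 0.5 is about 65% at 45 per arm and 70% at 50. Those are the reference values below.

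**Number of groups.** 50/10 = 5 groups at the largest permitted size and 50/2 = 25 at the smallest.

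**Variance inflation.** Take equal group size m, equal total variance σ² in both arms, n women per arm, and clustering in the intervention arm only.
- Variance of the intervention mean: (σ²/n)[1 + (m − 1)ICC]
- Variance of the control mean: σ²/n
- True over naive variance of the difference: V = [2 + (m − 1)ICC]/2
- True type I error at nominal 5%: 2[1 − Φ(1.96/√V)]

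Example for m = 10 and ICC = 0.10: V = (2 + 0.9)/2 = 1.45 and √V = 1.204, so the true standard error is 20% above the reported one. Then 1.96/1.204 = 1.628, and the type I error is 10.4%.

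The ICC is an assumption. For a baseline-adjusted analysis it is the ICC of the adjusted outcome. The simulated column is an ordinary t-test with 50 per arm and 20,000 runs per cell.

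| Group size | ICC | V | Type I error, formula | Type I error, simulated |
|---|---|---|---|---|
| 2 | 0.01 | 1.005 | 5.1% | 4.9% |
| 2 | 0.05 | 1.025 | 5.3% | 5.1% |
| 2 | 0.10 | 1.05 | 5.6% | 5.3% |
| 5 | 0.01 | 1.02 | 5.2% | 5.1% |
| 5 | 0.05 | 1.10 | 6.2% | 6.5% |
| 5 | 0.10 | 1.20 | 7.4% | 7.3% |
| 10 | 0.01 | 1.045 | 5.5% | 5.8% |
| 10 | 0.05 | 1.225 | 7.7% | 7.8% |
| 10 | 0.10 | 1.45 | 10.4% | 10.7% |

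At ICC = 0 the simulation returns about 5% for every group size, as it should.

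**Power of the planned test.** It barely moves. At d = 0.5 and 45 per arm, simulated power goes from 65% with no clustering to 63% with groups of 9 and ICC 0.10. The fault of the planned test is its error rate.

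**Power of a valid test.** As a simple stand-in for the mixed model, compare the intervention group means with the individual controls, using Welch–Satterthwaite degrees of freedom. With five groups of 10, d = 0.5 and 50 per arm, there are only about 10 to 17 degrees of freedom. Power is about 64% at ICC 0, 54% at ICC 0.05 and 46% at ICC 0.10, against about 70% for the ordinary test at ICC 0.

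**The case against.** The strongest reply is that the harm is conditional. Nothing in the article shows that the ICC is above zero. With pairs, or an ICC of 0.01, the inflation is a fraction of a percentage point up to about half a point, and the 10.4% figure needs every group at the maximum size. The sessions appear to share the same leaders and a fixed four-session curriculum, which removes one usual source of correlation. Clustering in one arm only also dilutes the effect. Finally, this is a condensed article, and random-effects structure is often left to a fuller document.

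Most of this stands as a limit on size. It does not rescue the tests. Peer interaction remains a plausible source of correlation and is the stated mechanism, groups of 10 are allowed, and no evidence is offered that the ICC is negligible. Nor is this a detail left open: the article names its tests and the families of covariates, and that choice does not match the delivery it describes.

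Three stronger readings are tempting and are not supported:
- **That type I error is inflated as a matter of fact, in every planned analysis.** The documents give no ICC. The questionnaire validation and the qualitative phase involve no between-arm test. Nothing in the article shows that preterm birth, caesarean section or NICU admission would correlate within discussion groups.
- **That the planned tests suffer both inflated error and a marked loss of power.** The marked loss belongs to a valid analysis; the planned one keeps its apparent power by understating the standard error.
- **That correcting the analysis is nearly free.** With about five large groups it is not.

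**Conclusion.** The point holds in conditional form. The named between-arm tests assume independence that the group delivery may break in the intervention arm. For any positive ICC the standard errors are too small. For ICC 0.01 to 0.10 at 50 per arm, the inflation is trivial with groups of 2, modest with groups of 5, and reaches about twice the nominal level with groups of 10.

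These figures rest on an assumed ICC, equal group sizes and equal total variance in the two arms. The case is strongest for the three primary scores. It should be fixed, but it does not undermine the design: randomisation, intervention and outcomes can stay as they are, provided group membership is recorded.

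**What to change.** 1. Record a session-group identifier for every intervention woman.
2. Replace the primary ANCOVA by a partially nested linear mixed model: random intercept for group in the intervention arm only, controls as singletons, and fixed effects for arm, baseline score and diabetes type. Use small-sample degrees of freedom (Satterthwaite, or Kenward–Roger in other software). SPSS MIXED can fit the model.
3. Use an analogous method for the other between-arm outcomes, such as a mixed model or group-robust errors for the binary ones, and report the ICC.
4. Fix the analysis code before the identifier is released. Only intervention women have a group, so the field reveals the arm to the analyst, who is meant to be blinded.
5. Restate the power with an assumed ICC and expected group size, applying the factor [2 + (m − 1)ICC]/2 and allowing for the limited degrees of freedom.

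The cost is one data field, revised wording, wider intervals and fewer degrees of freedom. The loss is small with many small groups but material with about five groups of 10, as the power figures above show. The sponsor should therefore know the likely number of groups before settling the restated power.

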#### Outcomes

The primary outcomes of the quantitative phase will include the mean scores of diabetes self-care activities, diabetes management self-efficacy, and pregnancy experience. The secondary outcomes will involve comparing the mean scores of satisfaction with antenatal care, rate of preterm birth, rate of cesarean section, neonatal hospitalization in the neonatal intensive care unit, breastfeeding performance score at 6 weeks postpartum, and validation of the SDSCA tool.

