#### Sample size

The sample size in this study was calculated based on the variable of diabetes self-care activities using the G-Power software. According to the results of the study by Al-Hashmi et al. [26] regarding the variable of diabetes self-care activities, and considering M_1_ = 3.1 and M_2_ = 3.7 (assuming a 25% increase due to intervention), SD_1_ = 1.2 and SD_2_ = 1.2, two-sided α = 0.05, and Power = 90%, the sample size was calculated to be 45 participants. Taking into account a 10% dropout rate, a final sample size of 50 participants in each group was considered.

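### Three unranked primary outcomes, one of them sized at the full two-sided 0.05, with no stated order or rule for a positive trial

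*Protocol article*

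**What the plan says.** The Outcomes section of the protocol article states: "The primary outcomes of the quantitative phase will include the mean scores of diabetes self-care activities, diabetes management self-efficacy, and pregnancy experience". The specific objectives of the quantitative phase give each of these three its own comparison between groups at weeks 36–39, adjusted for baseline. Neither place puts one above another.

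The Sample size section uses only one of the three: "The sample size in this study was calculated based on the variable of diabetes self-care activities". The error rate and power attached to it are "two-sided α = 0.05, and Power = 90%, the sample size was calculated to be 45 participants". The whole 0.05 is spent on that outcome.

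The Data analysis section begins the comparisons with "In the bivariate analysis, ANCOVA and the chi-square test will be employed" and lists the three primary outcomes together with the secondary ones. It then adds a general linear model adjusted for socio-demographic and obstetric characteristics, as a further exploration. It states no significance level, no order of testing and no rule for what makes the trial positive.

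**The concern.** Three primary outcomes of equal rank can support a trial conclusion in different ways. Any one of them may be enough, all may be required, or one may come first. The article does not choose. The any-one reading is open, and under it the primary conclusion is not held at 5%. The sample size calculation, in contrast, treats the trial as if it had one primary outcome at the full 0.05. The two sections describe different designs.

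What is at stake is how a mixed result is read. Suppose self-care activities show no difference and pregnancy experience does. The article as written would let this be reported as a positive primary result, although the trial was not sized on that outcome and the error rate for such a claim is not controlled. All three outcomes are participant-reported, and the Randomization and blinding section says that participants and outcome assessors know the allocation. A clear rule fixed in advance therefore matters all the more.

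**Working it through.** **Inputs from the protocol article**

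- Three primary outcomes (Outcomes; Specific objectives of the quantitative phase).
- Two-sided alpha 0.05 and power 90%, for self-care activities only (Sample size).
- Means 3.1 and 3.7, SD 1.2 in both groups, 45 per group before dropout, 50 after 10% dropout (Sample size).

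**Assumptions**

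- Each primary outcome is tested at 0.05. This is the only level stated, but it stands in the sample size section, not the analysis section.
- Any one significant outcome counts as success.
- All three null hypotheses are true.
- The test statistics share a common correlation r. The article gives none, so r runs from 0 to 0.9.

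**Step 1. The plan's own figure.** The standardised difference is (3.7 − 3.1)/1.2 = 0.5. The number per group for two-sided 0.05 and 90% power is 2 × (1.960 + 1.282)² / 0.5² = 84.1, so about 85. The stated 45 is not reproduced. At 45 per group the normal approximation gives 0.5 × √(45/2) − 1.960 = 0.412, which is a power of 66%; the t-test gives 65%. The dropout step is correct: 45/0.9 = 50.

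**Step 2. Family-wise error if independent.** 1 − 0.95³ = 1 − 0.857 = 0.143.

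**Step 3. Family-wise error if correlated.** This is one minus the probability that three equicorrelated standard normal statistics all lie within ±1.960:

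| Correlation r | Chance of at least one false positive |
|---|---|
| 0 | 14.3% |
| 0.3 | 13.6% |
| 0.5 | 12.5% |
| 0.7 | 10.9% |
| 0.9 | 8.4% |

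The rate stays above 5% over the whole range.

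**Step 4. If all three were required.** The family-wise error would then not exceed 5%. But the chance of success could be no higher than the power for self-care activities alone, and the sample size section takes no account of the other two. This reading does not fit that section either.

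**Step 5. Splitting alpha compared with ordering.** With a Bonferroni split (0.05/3 = 0.0167), t-test power for self-care activities at 45 per group falls from 65% to 47.6%. If self-care activities are tested first at the full 0.05, the 65% is kept. Most of the gap to 90% comes from Step 1 (90 − 65 = 25 points) rather than from the split (65 − 47.6 = 17.4 points).

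**The case against.** The strongest reply is that this is a condensed article. A multiplicity procedure is commonly left to the analysis plan, which is not shown, and the article nowhere says that each outcome is tested at 0.05 or that one success suffices. That is right as far as it goes: both are inferences, and the absence of a named adjustment method is not the point here. What stands is what the article itself fixes, namely three primaries without rank and a sample size that gives the full alpha to one. An analysis plan that divided alpha would contradict the sample size section.

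A second reply is that the three objectives may be three separate questions, each reported on its own. The family-wise figure would then not describe any single conclusion drawn. That reading is possible, but the article does not say so.

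A reader might also infer that there are at least four primary tests, because the Pregnancy Experience Scale has the domains hassles and uplifts. The independent-test figure would then be 1 − 0.95⁴ = 18.5%. The article does not support this. It names pregnancy experience as one outcome, reports an overall reliability for the scale, and nowhere says that the domains will be tested separately. Nor does it support the inference that every outcome has two chances of success, since the general linear model is described as further exploration.

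Finally, making self-care activities decisive can be questioned. The article reports a test-retest reliability of 0.40 for the SDSCA and says that it has not been validated in pregnant women with diabetes in Iran. This is a fair caution for the sponsor. It remains the outcome on which the trial was sized.

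**Conclusion.** The point holds in a limited form. The article names three primary outcomes of equal rank, sizes one at an undivided two-sided 0.05, and gives no order or success rule. If each is tested at 0.05 and any one counts, the family-wise error with all nulls true is about 14% if independent, 12.5% at correlation 0.5 and 8% at 0.9. A single figure of 13–14% would be too narrow, because it needs correlations of about 0.4 or less and the article gives none.

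The article permits the any-one reading but does not state it. This is a weakness in how the primary conclusion is defined, and it can be repaired cheaply before analysis. It is separate from the sample size problem in Step 1, which remains whichever rule is chosen.

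**What to change.** State in the protocol and the analysis plan that the baseline-adjusted ANCOVA of self-care activities (SDSCA) at weeks 36–39 is the first and decisive primary test, at two-sided 0.05. If it is significant, test self-efficacy and one pre-specified pregnancy-experience score, either in a stated fixed order at 0.05 or by Holm. If it is not significant, report those two with estimates and confidence intervals and make no confirmatory claim. Label the covariate-adjusted general linear model as supportive.

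This holds the family-wise error over the three outcomes at 5% and needs no extra participants. Holm over three equal primaries would also control the error and keep their equal rank, but self-care activities would then no longer be assured the full 0.05.

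The cost is that an effect on self-efficacy or pregnancy experience alone could no longer be claimed as a primary success. The trial is already registered, so the new hierarchy must be recorded as a dated registry amendment, made before outcome data are seen by group.

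The change leaves power where it is. The sample size section needs its own correction, because on its stated inputs 45 per group gives about 65% power.
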